## Abstract

**Background:**

International recommendations in favor of screening for vaginal infection in pregnancy are based on heterogeneous criteria. In most developed countries, the diagnosis of bacterial vaginosis is only recommended for women with high-risk of preterm birth. The Nugent score is currently used, but molecular quantification tools have recently been reported with a high sensitivity and specificity. Their value for reducing preterm birth rates and related complications remains unexplored. This trial was designed to assess the cost-effectiveness of a systematic screen-and-treat program based on a point-of-care technique for rapid molecular diagnosis, immediately followed by an appropriate antibiotic treatment, to detect the presence of abnormal vaginal flora (specifically, *Atopobium vaginae* and *Gardnerella vaginalis*) before 20 weeks of gestation in pregnant women in France. We hypothesized that this program would translate into significant reductions in both the rate of preterm births and the medical costs associated with preterm birth.

**Methods/Design:**

A multicenter, open-label randomized controlled trial (RCT) will be conducted in which 20 French obstetrics and gynecology centers will recruit eligible pregnant women at less than 20 weeks gestation with singleton pregnancy and with a low-risk factor for preterm birth. Interventions will include a) an experimental group that will receive a systematic rapid screen-and-treat program from a point-of-care analysis using a molecular quantification method and b) a control group that will receive usual care management. Randomization will be in a 1:1 allocation ratio. The primary endpoint that will be assessed over a period of 12 months will be the incremental cost-effectiveness ratio (ICER) expressed as cost per avoided preterm birth before 37 weeks. Secondary endpoints will include ICER per avoided preterm birth before 24, 28 and 32 weeks, obstetrical outcomes, neonatal outcomes, rates of treatment failure and recurrence episodes for positive women. Uncertainty surrounding these estimates will be addressed using nonparametric bootstrapping and represented using cost-effectiveness acceptability curves. A total of 6,800 pregnant women will be included.

**Discussion:**

This appropriate randomized controlled design will provide insight into the cost-effectiveness and therefore the potential cost savings of a rapid screen-and-treat strategy for molecular abnormal vaginal flora in pregnant women. National and international recommendations could be updated based on the findings of this study.

**Trial registration:**

ClinicalTrials.gov: NCT02288832 (registration date: 30 October 2014); Eudract: 2014-001559-22.

## Background

Prematurity is an important cause of death and disabilities of infants and children [1]. The preterm birth rate was approximately 7.4 % in France in 2010 [2], as observed in other developed countries [3]. The presence of infection and/or inflammation during pregnancy is notably known as a major risk factor for spontaneous preterm birth [4–6]. Pregnant women with bacterial vaginosis (BV) have an increased risk of preterm birth compared to women without BV, and the risk of preterm birth is higher if BV occurs in the early stage of pregnancy [5]. Several bacteria are associated with the diagnosis of BV [7]. However, BV is always associated with the presence of high loads of *Atopobium vaginae* and/or *Gardnerella vaginalis* [8, 9]. Our team previously showed that high vaginal concentrations of *A. vaginae* and/or *G. vaginalis* were associated with a significantly decreased interval between preterm labor and delivery in high-risk pregnancies [10, 11]. Therefore, the control of vaginal flora anomalies (especially *A. vaginae* and/or *G. vaginalis*) in low-risk populations should be considered as an important aim, to see whether their treatments might prevent preterm birth.

In France, the screening (and treatment) of BV is only recommended for women with high-risk of preterm birth [12, 13]. Because BV is asymptomatic in approximately 50 % of cases [14] and early vaginal infection during pregnancy induces higher risk of obstetrical complications, one of the measures to prevent preterm birth should concern a systematic screen-and-treat strategy at the first stage of pregnancy. The standard diagnostic test is the Nugent score [13], which is laborious and not easily reproducible [9]. Such abnormalities have led some authors to propose new diagnostic tools based on molecular biological techniques [7, 9, 15, 16]. The molecular approach based on the quantitative real-time polymerase chain reaction (qPCR) assay appears to be more reproducible and reclassifies a large number of flora rated as intermediate or normal on the Nugent score as true BV [6, 17].

Answering cost-effectiveness questions is a critical step in the translation of technological innovation findings into decision making at the public policy level. Although there is a considerable amount of literature on the economic consequences of preterm birth, little is known about the cost-effectiveness of screen-and-treat strategies for vaginal infection. To date, only one cost-effectiveness analysis of a simple screen-and-treat program for common asymptomatic vaginal infections in pregnancy has been published [18]: it showed cost savings through the first 6 years of life. In this study, the women were tested with a vaginal Gram stain and scoring criteria by the Nugent technique, which does not identify the morphotypes associated with BV such as *A. vaginae,* and the screening was performed in the second trimester of pregnancy, which is probably too late to prevent pregnancy complications.

All these considerations may lead to questions on the cost effectiveness of a systematic screen-and-treat program during the first trimester for flora vaginal anomalies among pregnant women with a low-risk of preterm birth, taking into account advances in diagnostic tools, bacteria species targeted and antibacterial treatments. For this purpose, a multicenter, randomized controlled study was designated to assess the cost effectiveness of the innovative screening for *A. vaginae* and *G. vaginalis* vaginal portage using a molecular quantification method by point-of-care with an appropriate treatment for positive cases, compared to a usual care strategy in pregnant women at less than 20 weeks of gestation. Several obstetrical and neonatal secondary outcomes are also considered, as well as rates of treatment failure and recurrence episodes.

## Methods/Design

### Design

A multicenter, open-label randomized controlled, two-parallel group study was designed in which pregnant women who attend prenatal care consultations before 20 weeks’ gestation at French obstetrics and gynecology centers are randomized between two management strategies: a systematic vaginosis screen-and-treat strategy (experimental group) and usual care management (control group). The study protocol was designed using the recommendations of the Consolidated Standards of Reporting Trials (CONSORT) statement and according to the guidelines of cost-effectiveness studies of the French Health Authority [Haute Autorité en Santé, Choix méthodologiques pour l’évaluation économique à la HAS http://www.has-sante.fr/portail/jcms/c_1120711/choix-methodologiques-pour-l-evaluation-economique-a-la-has]. Timing and phasing after eligibility checks are shown in Fig. 1.

**Fig. 1 Fig1:**
[figure not shown]
Schema of timing and phasing - AuTop Study

#### Inclusion and exclusion criteria

The details of the inclusion and exclusion criteria are provided in Table 2. The main inclusion criteria are that women must have less than 20 weeks of gestation, with singleton pregnancy, they must be symptomatic or nonsymptomatic with regard to their diagnosis of BV, and they must not have high-risk factors of preterm birth. The main exclusion criteria are having known conditions at the time of recruitment that have either increased risk of spontaneous preterm birth (previous preterm birth, uterine malformation, or multiple pregnancy) or that may need preterm delivery due to medical indication: hypertension, diabetes, fetal malformation, increased risk for preeclampsia (or other conditions that the investigators may consider).

**Table 2 Tab2:** Selection criteria

Inclusion criteria
Woman ≥ 18 years of age
Woman less than 20 weeks of gestation
Woman with singleton pregnancy
Woman without history of preterm birth or late miscarriage
Woman with low-risk factor of preterm birth (absence of diabetes, systemic lupus erythematosus, treated hypertension, fetal malformation, cervical conization, or multiple pregnancy)
Woman affiliated to or beneficiary of a social security system
Woman who have signed written informed consent
Exclusion criteria
Woman more than 20 weeks of gestation
Minor woman or woman deprived of their freedom by a court/administrative decision or woman under legal protection
Woman who present high-risk factor of preterm birth or late miscarriage
Woman with extrauterine pregnancy
Woman with non-evolutive pregnancy
Woman who have received antibiotic treatment in the week before inclusion
Woman misunderstanding the written and spoken French language
Subject participating in another biomedical research protocol

### Interventions

#### Experimental group: screen-and-treat strategy

Pregnant women assigned to the intervention group are asked for a self-collected vaginal swab at randomization (Time 0). The self-collected vaginal swab has previously been demonstrated to have high validity and reliability compared to a practitioner-collected swab [17]. The swab will be immediately tested for *A. vaginae* and *G. vaginalis* using a systematic point-of-care screening test. Quantitative molecular analyses will be performed in laboratories that have experienced and national accreditation to realize point-of-care techniques. The quantitative real-time PCR (qPCR) method used to diagnose BV was previously described [11]. The result is reported as copies of microorganism DNA per 1 mL of vaginal suspension [9]. According to previous works [9, 11], BV will be defined by an *A. vaginae* load ≥ 10^8^ copies/mL and/or a *G. vaginalis* load ≥ 10^9^ copies/mL. The conclusion will be feedback of the positive or negative test result to the practitioner within less than 24 hours. In cases of positive diagnosis, the pregnant woman will be referred to an obstetrician, and an appropriate antibiotic treatment will be provided. The first intention for treatment of *A. vaginae* and *G. vaginalis* will be azithromycin (single dose, 1 g at day 1 and 1 g at day 3). The second choice for antibiotic treatment will be amoxicillin 2 g per day during 7 days in cases of known intolerance of azithromicin. The following procedure for women who are diagnosed positive is to perform a series of three successive screening controls until 28 weeks to detect either the failure of antibiotic treatment or a recurrence (that is, reappearance of bacteria from a control vaginal swab after therapy is stopped) (see Fig. 1). In cases of recurrence or treatment failure, a new antibiotic treatment will be provided, based on protocol guidelines (see Fig. 2). For women with a first negative diagnosis, the usual care management will be proposed.

**Fig. 2 Fig2:**
[figure not shown]
Schema of treatment algorithm alongside the trial - AuTop Study

#### Control group: usual care management

No systematic vaginosis screening will be performed on the women assigned to the control group according to national and international guidelines [13, 19]. Usual pregnancy care includes 6 to 8 obstetrical consultations, no systematic vaginal swab, three ultrasound scans, 1st trimester Down syndrome screening and blood sampling for toxoplasmosis, syphilis, rubella, and complete blood group testing.

### Recruitment

Eligible women will be invited to take part in the study during a routine prenatal consultation planned in the first trimester of their pregnancy. The women who meet all the inclusion criteria will be randomized into one of the two groups after completing the informed consent form.

### Randomization

Computer-generated randomized lists were drawn up before the beginning of the study, using a permuted block design, under the responsibility of the clinical research unit (AP-HM). The randomization was stratified by center (1:1 allocation ratio).

### Endpoints

#### Primary endpoint

The primary endpoint is the incremental cost-effectiveness ratio (ICER), expressed as the extra cost per additional preterm birth avoided before 37 weeks. The effectiveness criterion has been discussed and consensually approved by all the study’s main partners (gynecologist coordinator and co-coordinators, biologists, health economist and methodologist). We can assume that this intermediary criterion properly reflects short- and long-term prognosis of the children [20, 21].

#### Secondary endpoints

The secondary endpoints are as follows:ICER per preterm birth avoided before 26, 28, 32 and 34 weeks.Obstetrical outcomes: rates of preterm birth before 26, 28, 32, 34, and 37 weeks of gestation, spontaneous abortion (between 14-22 weeks), late miscarriage (between 22-24 weeks), premature rupture of membranes, severe intrauterine growth restriction, preterm labor, duration of the woman’s hospitalization (that is hospitalization for delivery or preterm labor and potential previous hospitalizations due to gynecologic complications during pregnancy).Neonatal outcomes: neonatal mortality, neonatal morbidity (respiratory distress syndrome, bronchopulmonary dysplasia, necrotizing enterocolitis, periventricular leukomalacia), transfer to a neonatal intensive care unit (duration), mechanical ventilation (duration), congenital anomalies and duration of the newborn’s hospitalization.Treatment effectiveness: rate of recurrence (defined as a positive control vaginal swab using qPCR after the negativation of a precedent control vaginal swab), rate of treatment failure (defined as *A. vaginae* > 10^8^ copies/mL and/or a *G. vaginalis* load ≥ 10^9^ copies/mL from a control vaginal swab) and side effects associated with treatment.Other health care utilization: all the mother’s use of health care during the whole study period (for example, gynecologists and general practitioner consultations, hospital admission, clinical examinations and medications), as well as health care for the newborn (including neonatal care, re-hospitalization, medications, planned and non-planned consultations with pediatric practitioner or other specialists).

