### Statistical analysis

The data will be analyzed using SPSS version 20.0 software. Statistical significance is defined as *P* < 0.05. The methodology will be based on the Consolidated Standards of Reporting Trials Statement (CONSORT, http://www.consort-statement.org/consort-statement/) [26]. The full analysis population (including all subjects who will be randomized and will be at least evaluated at baseline) will be used in the primary analysis and the per protocol population (including all subjects who will be randomized and will not have major protocol deviations) will be used in the secondary analysis to assess the reliability of the results. Finally, missing data will be handled where possible using multiple imputations, and a sensitivity analysis will be performed. No interim analysis is planned.

The normality of the parameters will be estimated using frequency histograms and the Shapiro test. In case of nonparametric distribution, the data will be log transformed to obtain a normal distribution or nonparametric bootstrapping performed for cost data. In accordance with the distribution of the parameters, the baseline parameters will be presented separately for the control group and the experimental group: mean (standard deviation) or median (interquartile range) for continuous variables, proportions for categorical variables. Then, data will be compared between the two groups using Student’s t-test for continuous variables (durations), and chi-square or Fisher’s exact tests for categorical variables.

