### Cost-effectiveness analysis

Incremental cost-effectiveness ratios (ICER) will be used to compare the cost and effectiveness of the experimental strategy with usual care. The ICER is the ratio of the difference between groups in costs to the difference in effectiveness. The difference in effectiveness equals the number of preterm births averted and is calculated as the number of preterm births in the screening group minus the number of preterm births in the control group. Thus, the ICER provides information on the potential acceptability of the intervention for decision makers. The costs perspective taken in our economic analysis is that of the healthcare payer. The time horizon started from the first prenatal consultation before the 20 weeks of gestation and ended at 6-months of age or death. The healthcare costs included are those that are likely to differ across the intervention and control groups. In our study, these costs are those associated with: screening using the point-of-care procedure (quantitative molecular analysis), control vaginal swabs for positive women, antibiotic treatments, antenatal hospital admissions, physicians’ consultations, management of complications, as well as neonatal costs for full term infants and preterm infants. Unit costs for health service use will be estimated using data from the French National Hospital Database (Programme de médicalisation des systèmes d’information, PMSI) and the National Tariff. Treatment costs were obtained from the French register of pharmaceutical specialties, an online database of information on healthcare products. The cost of the POC analysis using quantitative real-time PCR (qPCR) will be calculated using micro-costing technique, which is particularly well suited to evaluating the cost of an emerging technique [27]. The volume of resources used will be determined by direct observation of each stage of each testing procedure. Fixed and variable costs will be included. All resources will be valued in 2015/2016 euros, and the 12-month trial means there is no requirement to apply discounting. As the cost of preterm birth differs significantly according to the gestational age at birth [28–30], we will attempt to address this issue by calculating an ICER for specific birth gestational ages. Probabilistic sensitivity analyses, using the non-parametric bootstrap method, will be carried out to generate mean expected ICERs and to determine whether uncertainty or variation in the data used affect the ICERs [31]. In addition, cost-effectiveness acceptability curves were constructed to represent decision uncertainty surrounding cost-effectiveness estimates [32].

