The third point concerns the delay between BV and treatment. In cases of late diagnosis, and therefore delayed treatment, BV has already been established and can lead to obstetrical complications involving preterm birth [41]. In this present study, we have considered that the point-of-care test will be an interesting approach to minimize the feedback of the vaginal swab to the practitioner in order to rapidly prescribe the antibiotic treatment in cases where tests are positive. In our trial, the short window for providing a diagnostic result also appears essential for minimizing the number of women lost to follow-up who may benefit from an early antibiotic treatment. Indeed, this rate of “lost to follow-up patients” is important in this disease where asymptomatic disease, anxiety and low socioeconomic status are clearly identified risk factors [9].

Finally, the gestational age at inclusion is the greatest limitation of previous published studies. Due to the lack of data concerning the early phase of pregnancy, the authors may have underestimated the effectiveness of a universal screen-and-treat program in reducing the rate of “very preterm birth” (28 to 32 weeks). These subdivisions into “very preterm” and “moderate” or “late preterm” (that is, 32 to less than 37 completed weeks of gestation) are important since decreasing gestational age is associated with increasing mortality, intensity of neonatal care required, and hence increasing costs [42].

The main purpose of AuTop trial is to support at a nationwide level the feasibility, acceptability, and cost-savings of a routine point-of-care molecular diagnosis at the first stage of pregnancy. Although it is well known that the consequences in terms of morbidity and mortality of preterm birth are important and entail a significant economic burden, several studies have demonstrated that a large share of the incremental cost per surviving preterm infant is represented by neonatal care [43, 44]. The average length of this neonatal care can vary from 3 days to 6 months for very preterm births (including potential immediate re-hospitalization, programmed consultations and bronchiolitis prevention measures). We then decided to focus on this time horizon for the cost-effectiveness analysis.

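### Late neonatal morbidities and the three newborn durations are compared by simple tests that do not treat death as a competing outcome, and listed mortality is neonatal only

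*Protocol article*

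**What the plan says.** The Secondary endpoints section of the protocol article names the neonatal outcomes as separate items: "neonatal mortality, neonatal morbidity (respiratory distress syndrome, bronchopulmonary dysplasia, necrotizing enterocolitis, periventricular leukomalacia), transfer to a neonatal intensive care unit (duration"). The same sentence continues with "mechanical ventilation (duration), congenital anomalies and duration of the newborn"'s hospital stay. Mortality is thus one item among several. The durations in intensive care, on ventilation and in hospital stand on their own.

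The Statistical analysis section fixes the tests in one line: Student's "t-test for continuous variables (durations), and chi-square or" Fisher's exact tests for categorical variables. On incomplete data it says only that "missing data will be handled where possible using multiple imputations".

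The Cost-effectiveness analysis section takes the healthcare payer's view. Its time horizon "ended at 6-months of age or death". The Discussion supports that horizon by noting that the average length of neonatal care "can vary from 3 days to 6 months for very preterm births".

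**The concern.** Death precludes the later outcomes. An infant who dies in the first days has a short stay and few days on a ventilator, and has no time to develop bronchopulmonary dysplasia or the other late conditions. If such infants enter the comparison with those values, the arm with more early deaths tends to show shorter stays and less late morbidity. The reverse is equally possible. If screening turned some early deaths into survival after long intensive care, the screened arm would look worse on these outcomes because more infants lived.

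The second gap is the mortality window. The study follows infants and their costs to 6 months, and the Discussion expects some very preterm infants to need care for that long. A death after the neonatal period falls outside the listed mortality outcome, although it ends the stay and the accrual of cost.

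At stake is the reading of the secondary neonatal results, which describe how the children fared beyond the rate of preterm birth.

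**Working it through.** No figure in the plan bears on this point, so there is none to reproduce. The check is of direction, with assumed values where the document gives none.

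**Scale of the trial.** From the Sample size section: 3,400 women per arm with 20% lost leaves 3,400 × 0.8 = 2,720. Expected preterm births are 2,720 × 0.043 ≈ 117 in the control arm and 2,720 × 0.030 ≈ 82 in the screened arm. The document gives neither a mortality rate nor a distribution of stay.

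**Durations.** Assume that survivors of a high-care group stay 40 days and that infants who die do so on day 2. With a proportion q dying, mean stay = 40(1 − q) + 2q.

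| q | Mean stay (days) |
|---|---|
| 5% | 38.1 |
| 10% | 36.2 |
| 20% | 32.4 |

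Survivors' care is identical in every row. An arm with 10% deaths against 5% looks better by 1.9 days. At 20% against 5% the apparent gain is 5.7 days. At equal q it is zero.

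**Dependence on the denominator.** If all infants are counted, an excess of 0.5 to 2 early deaths per 1,000, each removing 30 to 90 days (assumed), shifts mean stay by 0.0005 × 30 = 0.015 to 0.002 × 90 = 0.18 days. The shift is small over all births and can reach days only within a high-care subgroup. The article does not say which denominator applies.

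**Late morbidity.** Let r be the risk of a late condition among survivors, the same in both arms, and let infants who die early contribute no case. The observed rate is r(1− q). The ratio between an arm with q = 10% and one with q = 5% is 0.90/0.95 = 0.947. For 20% against 5% it is 0.80/0.95 = 0.842. Observed morbidity therefore falls by about 5% to 16% in relative terms with no change in survivors' risk. The composite rate q + r(1 − q) = r + q(1 − r) rises with q, so the composite does not reward death.

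**Days alive and out of hospital.** In the same example, counted to 180 days (6 × 30), a survivor scores 180 − 40 = 140 and a death scores 0. The means are 0.95 × 140 = 133, 0.90 × 140 = 126 and 0.80 × 140 = 112. The ordering now agrees with mortality.

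**Mortality window.** The listed outcome is neonatal mortality, while the cost horizon is 6 months of age or death. The 6-month questionnaire (Table 3) asks for all of the infant's health outcomes, so later deaths can be captured, but no listed mortality outcome contains them.

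**The case against.** The strongest reply is that a journal article condenses the protocol, and that denominators and the coding of deaths belong in an analysis plan that is not shown. Part of this stands: the article does not say that deaths are coded as short stays or as free of morbidity, so the misreading is possible rather than certain. But the article does fix the tests and the form of the outcomes. Restricting them to survivors would not be a full remedy either, since survival is itself a result of what follows randomization, and the survivors of two arms with different mortality are not comparable groups.

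A reader might infer that the plan ignores death altogether. It does not: neonatal mortality is the first neonatal outcome listed, fetal death is collected at delivery, and the cost horizon names death. Nor does an early death pass for a healthy infant on every outcome. Respiratory distress, transfer to intensive care and the need for ventilation can still register, and a preterm infant who dies still counts as a preterm birth.

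A reader might also infer that ending costs at death distorts the cost-effectiveness ratio. The documents do not support that. A payer bears no further care cost for an infant who has died, and preterm birth as the unit of effect is a declared choice argued under Primary endpoint. The large effect that one costly infant can have on a mean cost is sampling variability, which the planned bootstrap addresses. It is not evidence of bias.

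Finally, under the planned hypothesis the screened arm has fewer preterm births and so, plausibly, fewer deaths. Truncation by death would then work against the intervention. That is fair, and it means that the direction cannot be assumed in advance.

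**Conclusion.** The point holds for the late morbidities, the three newborn durations and the mortality window. It does not extend to the primary ratio or to the costing rule.

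Its size cannot be derived from the document. The shift requires a mortality difference between the arms, by effect or by chance, and depends on which infants form the denominator. With about 117 and 82 preterm births expected in a low-risk population, deaths should be few and the practical effect is probably modest. The figures in days and the relative rates above rest on assumed values and show direction only. This is an inexpensive improvement to secondary analyses, not a flaw that threatens the trial.

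**What to change.** 1. Analyse each late morbidity (dysplasia, enterocolitis, leukomalacia) also as death or the condition.
2. Analyse the three durations as days alive and out of hospital, out of intensive care and off ventilation up to a fixed age, with death scored as the worst value.
3. Add infant death to 6 months as a secondary outcome.
4. Show infant deaths by arm beside the cost-effectiveness ratio, and leave the cost horizon as it is.

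The cost is a few lines of analysis text and some derived variables. Dates of death and discharge are already needed for the stated horizon. There are two downsides. Composites mix death with morbidity, so each component must be reported as well. The fixed age also needs a choice: 6 months covers the longest stays but leans on the mothers' questionnaire, while a shorter window depends less on it and cuts those stays off.

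### The treatment-failure endpoint sets no swab order, so it also counts essentially every recurrence and mixes non-clearance with relapse

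*Protocol article*

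**What the plan says.** Women who screen positive in the experimental group are treated and then followed with control swabs. The section on the experimental group has the sites "perform a series of three successive screening controls until 28 weeks", the purpose being "to detect either the failure of antibiotic treatment or a recurrence". It explains recurrence in passing as "reappearance of bacteria from a control vaginal swab after therapy is stopped". Positivity is fixed in the same paragraph: "BV will be defined by an *A. vaginae* load ≥ 10^8^ copies/mL and/or a *G. vaginalis* load ≥ 10^9^ copies/mL".

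The Secondary endpoints section then gives two separate rates, one after the other. It lists recurrence, "defined as a positive control vaginal swab using qPCR after the negativation of a precedent control vaginal swab), rate of treatment failure". The second of these, treatment failure, is an *A. vaginae* load above 10^8 and/or a *G. vaginalis* load of at least 10^9 "copies/mL from a control vaginal swab) and side effects associated with treatment". The failure definition carries no condition on timing, on the order of the swabs, or on earlier negative results.

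**The concern.** The intervention text presents failure and recurrence as alternatives, and the endpoint list gives each its own rate. A failure definition met by any control swab cannot keep them apart: a woman who cleared the bacteria and relapsed weeks later has a control swab at threshold and so counts as a failure as well.

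The two events say different things about the programme. Failure to clear concerns the antibiotic course; relapse after clearance concerns the durability of its effect and the value of repeat testing. The Discussion criticises earlier work because few studies controlled for treatment efficacy and most ignored recurrence. A failure rate that absorbs relapse would understate initial clearance, on a point the trial sets out to improve.

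Two smaller discrepancies sit beside this. The *A. vaginae* cut-off is strictly greater than 10^8 for failure but at least 10^8 for diagnosis. The recurrence wording in the intervention text names neither a prior negative control swab nor a load, whereas the endpoint definition requires the negative swab.

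**Working it through.** The document states no expected failure or recurrence rate for the trial, so there is no figure to reproduce. The check has two parts.

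**1. Logic of the definitions.** Write the three control swabs as 1 (positive) or 0 (negative). There are 2^3 = 8 patterns.

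- Failure as written (any positive control swab): 001, 010, 011, 100, 101, 110, 111, which is 7 of 8.
- Recurrence as written (a positive after a negative): 001, 010, 011, 101, which is 4 of 8.
- Overlap: all 4 recurrence patterns are among the 7 failure patterns.
- Positive at the first control swab (the first course did not clear): 100, 101, 110, 111, which is 4 of 8.

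The failure definition therefore adds 001, 010 and 011, which are women whose first control was negative. Pattern 101 belongs in both categories, as two separate events. The only recurrence that escapes the failure definition is a swab positive solely through *A. vaginae* at exactly 10^8 copies/mL, because of the > versus ≥ mismatch; this has no practical weight.

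**2. Illustrative size.** Inputs:

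- Women treated: 10% of 3,400 = 340 (Sample size).
- r, recurrence among women who cleared: 28% to 50% (Discussion, background literature).
- f, true failure at the first control swab: 10%, 20% or 30%. **This is an assumption; the documents give no value.**

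Literal failure rate = f + (1 − f) × r.

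| f | r = 28% | r = 50% | True failures | Counted as failures | Relapses added |
|---|---|---|---|---|---|
| 10% | 0.10 + 0.90 × 0.28 = 35.2% | 0.10 + 0.90 × 0.50 = 55.0% | 34 | 120 to 187 | 86 to 153 |
| 20% | 0.20 + 0.80 × 0.28 = 42.4% | 0.20 + 0.80 × 0.50 = 60.0% | 68 | 144 to 204 | 76 to 136 |
| 30% | 0.30 + 0.70 × 0.28 = 49.6% | 0.30 + 0.70 × 0.50 = 65.0% | 102 | 169 to 221 | 67 to 119 |

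The inflation is (1 − f) × r, from 0.70 × 0.28 = 19.6 to 0.90 × 0.50 = 45.0 percentage points. The 3,400 includes the allowance for 20% loss to follow-up. If that loss applied evenly, 340 would become 340 × 0.80 = 272; the head counts would shrink in proportion and the percentages would not change.

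**The case against.** The best defence is that the intent is plain. The intervention text sets failure against recurrence, the endpoints list them separately, and next to a recurrence defined by a prior negative swab, failure can naturally be read as a swab that never turned negative. The treatment algorithm (Fig. 2) is not shown and may hold the operational rule. A condensed article may also leave swab-level derivation and denominators to the full protocol or analysis plan.

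Part of this stands. Denominators are not raised here, and Fig. 2 may well settle the sequence. But the article does not leave failure undefined. It states a rule, and applied as written that rule gives a rate that departs from the evident intent. If another document has the sequence right, this definition still has to match it.

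Several stronger conclusions might be drawn, and the documents do not support them:

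- *That both rates are wrong.* The recurrence endpoint is coherent as it stands; only failure is inflated.
- *That the intervention text sets up a rival recurrence endpoint under which a persistently positive woman recurs.* Reappearance implies earlier clearance, and the same paragraph defines positivity. It reads as a loose paraphrase.
- *That the two events cannot be separated.* The swab series allows it; only the label is at fault.
- *That the economic result is distorted.* Control swabs and antibiotics are costed as such, not by failure or recurrence label.

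**Conclusion.** The concern holds for the failure rate. As defined, it includes essentially every recurrence (4 of 4 patterns, apart from the exact-threshold case) and would report non-clearance and relapse as one figure.

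The size cannot be fixed from the documents. With true failure assumed at 10-30% and the background 28-50% recurrence applied to women who cleared, the reported rate would be about 35-65%. The 28-50% is not a forecast for this regimen and swab schedule; the Discussion itself says that it varies with the treatment and the time since intake. The direction of the error does not depend on these values: any relapse after a negative first control raises the failure rate.

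The reach is limited. This is a descriptive secondary endpoint in screen-positive women of one arm, and the primary endpoint is not affected through it. The change is still worth making, because the trial presents control of treatment efficacy and recurrence as an advance on earlier studies.

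**What to change.** Define both events per treatment course, so that each positive control swab carries exactly one label:

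- **Failure of a course:** a positive control swab with no negative control swab since that course, the course being the most recent one.
- **Recurrence:** a positive control swab after at least one negative control swab since the most recent course.

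Tying the labels to the course matters. Take a woman who is negative, then positive and retreated, then positive again. Rules that look only at the whole series could call her third swab both a failure and a recurrence. Under the wording above, the second swab is a recurrence after the first course and the third is a failure of the second course. A woman may have both as distinct events. Report the first-course failure rate separately; over three control swabs it corresponds to patterns 100, 101, 110 and 111.

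Use one positivity threshold throughout by reconciling the > 10^8 and ≥ 10^8 for *A. vaginae*, and align the recurrence wording in the experimental-group section with the endpoint definition.

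The cost is a change of wording. The planned control swabs supply all the data, and no treatment rule, visit or sample size changes.
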